### 2.12. Limitations and Contingency Plan

#### 2.12.1. Limitations

The study uses a single-blind design because participants cannot be blinded to nut consumption. This may introduce expectancy bias, but it is mitigated by blinding outcome researchers. Primary mental health outcomes rely on self-report questionnaires and are therefore subject to reporting biases. However, validated instruments and complementary objective measures, such as cognitive tests and biomarkers, are included. Adherence cannot be directly observed in free-living conditions. Monitoring through biweekly contact and determination of vitamin E blood concentrations at each visit improves, but does not guarantee, compliance and does not prevent contamination of the control group. The sample consists of university students aged 18–24 years from a single campus. This limits generalizability but enhances internal validity in an understudied population. The study may be underpowered for small effects, secondary outcomes, or subgroup analyses, particularly if dropout exceeds the anticipated 20%. Finally, the 6-month intervention and follow-up period may be insufficient to assess long-term or delayed effects.

The extensive assessment protocol may increase participant burden and the risk of attrition. Although a validated FFQ will be used, dietary assessment remains imprecise and is subject to underreporting and recall bias. Additionally, some control group participants may live with participants from other study groups, which makes complete prevention of contamination unrealistic. While the CG will be instructed to avoid nuts from any source and the IG-30 and IG-60 groups will be instructed to avoid nuts from non-study sources, accidental or intentional nut consumption may still occur.

Finally, academic stressors (e.g., exams, tight assignment deadlines) and seasonal variations may affect mental health and thereby influence the study associations.

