### 2.6. Randomization and Allocation Processes

The randomization and allocation processes will occur before the baseline assessment. To ensure balance across study arms, randomization will be stratified by sex considering the ratio of 2 males:3 females, since this is the ratio observed in the reference population of university students on the campus of Cuenca of the UCLM. Allocation concealment will be maintained using sequentially numbered, opaque, sealed envelopes, which will be opened only at the point of assignment. To minimize selection bias, the allocation sequence will remain concealed from the research team until the end of the intervention (six months). Participants will be informed of their group allocation immediately after the randomization procedure has been completed.

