### 2.7. Intervention Implementation

Once randomization is complete, participants will receive printed and verbal standardized instructions to maintain their usual lifestyle habits throughout the study period, except for nut consumption, where the following group-specific instructions will be provided:Control group (CG): Participants will be instructed to continue their habitual diet while avoiding direct nut consumption, although the sporadic consumption of foods that may contain trace amounts of nuts as ingredients (e.g., baked goods, ice cream) does not constitute a protocol violation.Intervention groups (IG-30 and IG-60): Participants will be instructed to consume 30 g or 60 g of unsalted, unroasted mixed nuts daily and to exclusively consume the amount of nuts provided by the researchers, refraining from consuming other sources of nuts. For the participants in the CG, sporadic exposure to trace amounts of nuts in processed foods (e.g., baked goods, ice cream) will be acceptable.

The nuts (a mixture of almonds, walnuts, pistachios, and hazelnuts) will be provided free of charge, in daily portions, to participants in the intervention groups for the full duration of the trial. The participants will be asked to incorporate nuts into their usual diet and to consume them in any uncooked manner they prefer, such as alone (only nuts), with salad, or yogurt.

At months 2 and 4, participants will be instructed to collect the prepacked bags containing the daily portions of nuts required for each intervention group during the subsequent period (i.e., participants in IG-30 will receive 30 g bags, and those in IG-60 will receive 60 g bags). To maintain a single-blind design, the nuts will be provided in person for each participant by a researcher who is not involved in clinical assessments. The bags containing the daily content of nuts will be specifically produced for the trial in accordance with established quality standards and sealed under a protective atmosphere. Each bag will contain a fixed mixture of nuts in the following proportions: 35% almond, 35% walnut, 20% unshelled pistachios, and 10% hazelnut. These nut mix proportions are based on the most consumed nut types in Spain and were designed to provide a balanced profile of fatty acids, micronutrients, and bioactive compounds while reflecting habitual intake, improving palatability and adherence, and facilitating translation into practical dietary recommendations.

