#### 2.10.1. Primary Mental Health Outcome Measures

Depressive symptoms: The assessment of depressive symptomatology will be conducted using the Beck Depression Inventory–II (BDI-II) [63], a widely validated 21-item self-report measure designed to evaluate the severity of depressive symptoms over the preceding two weeks. Each item offers four response options scored from 0 to 3, with higher scores reflecting greater depressive severity. The BDI-II is considered the gold-standard screening instrument for individuals aged 13 years and older [64]. The Spanish version of the BDI-II has previously been validated [64] and has demonstrated good internal consistency (Cronbach’s α = 0.89) and strong construct and criterion validity across university students [65]. The total scores range from 0–63 and are derived from the sum of all 21 items. Conventional cutoffs classify symptom severity as minimal or absent (0–13), mild (14–19), moderate (20–28), or severe (29–63).

Anxiety symptoms: Anxiety symptoms will be assessed using the Generalized Anxiety Disorder 7-item scale (GAD-7) [66], a validated self-report instrument developed to screen for and quantify the severity of generalized anxiety symptoms over the preceding two weeks. The participants rated each item on a four-point scale ranging from 0 (“not at all”) to 3 (“nearly every day”), yielding a total score between 0 and 21. Higher scores indicate greater anxiety symptomatology, with established cutoffs categorizing symptom severity as mild (5–9), moderate (10–14), or severe (15–21) proposed [66]. The Spanish version of the GAD-7 [67] shows excellent reliability values (Cronbach’s α = 0.94) and good accuracy in identifying cases of GAD (sensitivity and specificity > 0.80) [66,67], including among university students (Cronbach’s α = 0.90) [68].

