Limitations include the inability to blind participants due to the whole-food nature of the intervention, which may introduce performance or expectation bias. To minimize these biases, a multi-layer strategy will be implemented. First, allocation will be strictly concealed using opaque, sealed envelopes until baseline assessments are completed. Following randomization, outcome assessors and data analysts will remain blinded to group allocation throughout the trial. During the intervention period, compliance will be monitored via blood vitamin E concentrations. At assessment points, self-reported mental health measures (BDI-II, GAD-7) will be complemented with objective cognitive assessments (NIH Toolbox) and biological markers (BDNF, inflammatory markers, cortisol). Together, these measures help mitigate expectancy effects and strengthen the trial’s internal validity. The recruitment of university students enhances sample homogeneity but may also restrict the generalizability of the findings to broader young adult populations. Finally, although the study is powered to detect medium effect sizes, mental health outcomes are multifactorial and may be influenced by unmeasured genetic or environmental factors.

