## Figures and Tables

**Figure 1 healthcare-14-00435-f001:**
[figure not shown]
Planned study design.

**Table 1 healthcare-14-00435-t001:** Data collection methods and measurement protocols for the study variables in the Nuts4Brain-RCT study.

Outcomes			
Group of variables	Outcomes	Scales or measurement procedures	Collection methods
Primary mental health outcome measures	Depression	BDI-II	Tablet self-report
	Anxiety	GAD-7 questionnaire	
	Stress	PSS-10	
	Cognitive functioning	Flanker, DCCS, PSM, LSWM, PC	Tablet application guided by researcher
Secondary mental health outcome variables	Risk of eating disorders	SCOFF questionnaire	Tablet self-report
	Body image perception	SFS	
	Resilience	CD-RISC-10	
	Quality of Life	SF-12 Health Survey	
	Sleep quality	PSQI	
Potential confounding, mediating, and moderating factors			
Socioeconomic level	Socioeconomic Status	SES	Tablet self-report
Demographic features	Birth date, sex, gender, marital status, type of housing, and, for female participants, breastfeeding, and menstrual status.	Ad hoc questionnaire	
Medical history	Medication and family history of mental or cardiovascular disorders		
Anthropometry	Height, weight, waist circumference	Anthropometry tests	Physical measurement
Body composition	Fat mass, lean mass	Bioelectrical impedance analysis	
	Fat mass, lean mass, bone mineral density, bone mineral content	Dual-energy X-ray absorptiometry	
Lifestyle behaviors	Food consumption and nutrient intake	Food frequency questionnaire-137	Paper self-report
	Nut consumption	Ad hoc questionnaire	Tablet self-report
	Adherence to the Mediterranean diet and its specific components	MEDAS questionnaire	
	Screen time	Ad hoc questionnaire	
	Social media addiction	ARS-6	
	Problematic substance use	ASSIST	
	Physical activity	IPAQ	
Health-related variables	Cardiorespiratory fitness, agility and speed, muscular strength, flexibility, overall physical fitness	IFIS	
	Muscular strength	Standing long jump and handgrip strength tests	Physical measurement
	Blood pressure	Blood pressure test	
	BDNF	Blood tests ELISA	Blood biochemical parameters
	Hemogram, total cholesterol, HDL-c, LDL-c, triglycerides, glucose, insulin, HbA1c, vitamin D, vitamin E, vitamin B12, folic acid, iron, magnesium, IL-6 and hs-CRP.	Blood tests	

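### Blinding the outcome researchers cannot mitigate expectancy bias on BDI-II, GAD-7 and PSS-10, which participants who know their arm rate themselves

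*Protocol article*

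**What the plan says.** Section 2.12.1 (Limitations) states: "The study uses a single-blind design because participants cannot be blinded to nut consumption". It continues: "This may introduce expectancy bias, but it is mitigated by blinding outcome researchers". The Discussion (section 3) lists concealed allocation, blinded assessors and analysts, vitamin E monitoring, cognitive tests and biological markers, and concludes: "Together, these measures help mitigate expectancy effects".

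Other sections fix who produces the scores and what each arm receives:

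- **Outcomes.** Section 2.10.1 lists four primary outcomes. It describes BDI-II as "a widely validated 21-item self-report measure designed to evaluate the severity of depressive symptoms over the preceding two weeks", and GAD-7 and PSS-10 as self-report scales too. Table 1 gives the collection method for all three as "Tablet self-report". Only the NIH Toolbox tests are guided by a researcher.
- **Knowledge of the arm.** Section 2.6 says: "The randomization and allocation processes will occur before the baseline assessment". It adds: "Participants will be informed of their group allocation immediately after the randomization procedure has been completed".
- **Arm differences.** Section 2.7 gives the intervention groups free nuts, handed over in person by a researcher who makes no assessments: "At months 2 and 4, participants will be instructed to collect the prepacked bags". Controls are told to avoid nuts, and no corresponding contact is described for them.

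**The concern.** Assessor blinding works by keeping the person who produces the score unaware of the arm. For the three questionnaires that person is the participant, who is told the arm. Blinding a researcher who does not produce the score leaves the participant's expectation untouched.

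The other safeguards in the Discussion do not fill the gap. Vitamin E speaks to adherence. Cognitive tests and biomarkers are different outcomes. They can show whether a self-rated benefit has objective support, but they do not change a BDI-II, GAD-7 or PSS-10 score.

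Each nut-versus-control contrast on these scales therefore estimates the effect of nuts together with expectancy and with the attention and reward of being given food in person. Section 2.11 makes these contrasts its post hoc comparisons and means to discuss implications for guidelines. It also says that small but consistent effects, and changes short of significance, may matter. Small shifts are what expectancy could plausibly produce. A reader who relies on section 2.12.1 would think this had been dealt with.

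**Working it through.** **1. Which primary outcomes can assessor blinding reach?**

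| Primary outcome (2.10.1) | Who produces the score | What assessor blinding can do |
|---|---|---|
| BDI-II | Participant, on tablet | Nothing |
| GAD-7 | Participant, on tablet | Nothing |
| PSS-10 | Participant, on tablet | Nothing |
| NIH Toolbox | Participant's performance, guided by staff | Limit assessor bias, not participant expectancy |

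Three of four are out of reach. The abstract also names BDNF as primary, which would make it three of five.

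**2. When is the arm known?** Section 2.6 randomizes before the baseline assessment and discloses the arm at once. The Discussion says allocation stays concealed until baseline assessments are complete. Both cannot hold. If section 2.6 is followed, baseline self-ratings may also be made with knowledge of the arm.

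**3. How far could a spurious shift mislead?** The inputs from section 2.4 are 42 evaluable participants per group, SD = 1 and two-sided alpha 0.05. The plan's enrolment follows from the 42: 42 / (1 − 0.20) = 52.5, rounded up to 53 per group, and 3 × 53 = 159. Whether 42 itself follows from a two-sided alpha is a separate question; it is used here as stated.

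The documents give no size for expectancy, so the shift δ is **assumed** at 0.1, 0.2 and 0.3 SD, with no true nut effect.

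Standard error of one contrast: √(2/42) = 0.218 SD.

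Chance of significance: Φ(δ/SE − 1.96) + Φ(−δ/SE − 1.96).

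| δ (SD) | δ/SE | Calculation | Chance of significance |
|---|---|---|---|
| 0 | 0 | 0.025 + 0.025 | 5% |
| 0.1 | 0.46 | 0.067 + 0.008 | about 7% |
| 0.2 | 0.92 | 0.148 + 0.002 | about 15% |
| 0.3 | 1.37 | 0.279 + 0.0004 | about 28% |

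The first term is the chance of a result favouring nuts, so the excess lies almost wholly in that direction.

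**4. Check with the plan's multiplicity rule.** Both nut arms were simulated against the shared control (test statistics correlated 0.5) with the same shift in each. The two-sided Benjamini–Hochberg rule was applied on one scale, declaring at least one difference if the smaller p ≤ 0.025 or the larger p ≤ 0.05. The chance of at least one significant contrast with 42 per arm was 4.8%, 7.6%, 16% and 31% for shifts of 0, 0.1, 0.2 and 0.3 SD. The abstract gives 135 participants rather than 159; that leaves 135/3 × 0.8 = 36 per arm, and the three non-zero shifts give 7.1%, 15% and 28%. The picture is the same.

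**The case against.** The strongest reply is that the weakness is largely disclosed. Section 2.12.1 says outright that participants are unblinded and that the primary mental health outcomes are open to reporting bias, and the Discussion repeats the risk of expectation bias. The text claims mitigation, not removal, and calls the objective measures complementary. That is fair as disclosure. It does not rescue the sentence on assessor blinding, which names a mechanism that cannot operate on a self-rated score. A fuller protocol or analysis plan could not make it true either.

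The design also holds a partial internal check. IG-30 and IG-60 both receive free nuts, the same hand-overs and the same messages, so their comparison is matched on reward and attention. Dose-related expectancy may remain, but the full concern applies only to the contrasts with control.

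The calculation is generic: the shifts are assumed, and a two-sample test is simpler than the planned mixed model. Both points stand. The figures show sensitivity, not a forecast.

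A reader might infer more than the documents support:

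- **That individualized support for poor adherence goes only to the nut arms.** Section 2.12.2 offers it to participants in whom poor adherence is detected, without naming an arm. Controls also have an adherence rule, and the same section describes how breaches of it are detected.
- **That the fortnightly message is the only contact all arms share.** Standardized instructions (2.7) and assessment visits of about three hours at baseline, 3, 6 and 12 months (2.9, 2.10) are given without distinction by arm. The documented difference is the free nuts and their hand-over.
- **That controls certainly have no matching contact.** The article describes none, but does not expressly exclude one.

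**Conclusion.** The point holds for the stated protection. Assessor blinding gives BDI-II, GAD-7 and PSS-10 no protection against expectancy, and the cognitive tests and biomarkers do not correct those scores. This follows from who rates the scales and needs no numerical assumption.

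The size rests on the assumed shifts, on no true nut effect, and on 42 per arm with SD 1: about 7%, 15% or 28% significant per nut-versus-control contrast instead of 5%. If expectancy is negligible there is no inflation, and the documents cannot settle which case applies.

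Participant blinding is not feasible and its absence is no fault. Nor does the point invalidate the trial. It limits what a self-rated benefit over control can be said to show, and the plan should say so.

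**What to change.** 1. **Wording.** In section 2.12.1 and the Discussion, replace the mitigation claim with a statement that expectancy is not controlled for BDI-II, GAD-7 and PSS-10, that assessor blinding guards only against assessor bias in the researcher-guided tests, and that objective measures aid interpretation. This stands alone even if the rest is declined.
2. **Interpretation.** State in section 2.11 that a self-rated benefit over control includes any effect of expectancy and attention. Note that IG-30 versus IG-60 is matched on free food and hand-overs, although dose-related expectancy may remain.
3. **Timing.** Reconcile section 2.6 with the Discussion on whether the arm is disclosed before or after baseline.
4. **Expectancy items.** Ask two brief questions before randomization: the expected effect on mood of eating nuts, and of avoiding them. Under section 2.6 as written, the baseline visit would be too late. Report the answers descriptively by arm. An arm-by-expectancy interaction would be too imprecise to test: with residual SD 1 and expectancy standardized (assumed), the slope difference has SE of about 0.22, so 80% power needs about 2.8 × 0.218 = 0.61 SD per SD of expectancy, more than the design effect of 0.5.
5. **Contact.** Give controls a brief matched contact at months 2 and 4 from the researcher who distributes the nuts.

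**Cost.** Text changes, plus a few minutes of participant and existing staff time. The items need a short step before randomization. The article describes itself as written before recruitment, so nothing already collected is affected.

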### 2.3. Eligibility Criteria

The inclusion criteria will be as follows: (1) being enrolled as a university student in any undergraduate academic program at the University of Castilla-La Mancha (UCLM), campus of Cuenca; (2) aged between 18 and 24 years; and (3) being willing and able to provide written informed consent to participate.

The exclusion criteria will include any known food allergies, particularly tree nuts or peanuts; chronic psychiatric or gastrointestinal medical conditions diagnosed and/or under pharmacological treatment; and the expected inability to attend follow-up visits because of planned internship abroad or study completion during the trial period. Those who are pregnant at the time of randomization or who plan to become pregnant during the follow-up period will be ineligible.

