### 2.4. Sample Size Calculation

The sample size was calculated using the Grayling and Wason method for multi-arm trials [56], which is appropriate for a design with two experimental groups and one control group. A medium effect size (Cohen’s d = 0.5) and homogeneity of variance (σ = 1) were assumed across groups as recommended [57] when no clear estimate on this association is provided in the available studies with similar design [48,49]. With a two-sided α of 0.05 and 80% power (β = 0.20), the required sample size was obtained via the “des_ss_norm()” function in R statistical software, version 4.5.2 (R Core Team, 2024, Vienna, Austria). All three arms were allocated at a 1:1:1 ratio. To account for multiple comparisons, the Benjamini–Hochberg correction was applied to control the false discovery rate. The power calculation was based on a disjunctive criterion, which estimates the probability of detecting at least one significant difference between any intervention group and the control group. The initial calculation yielded a requirement of 42 participants per group. After accounting for an anticipated 20% dropout rate, the final sample size was adjusted to 53 participants per group. This resulted in a total target enrollment of 159 participants across all three study arms. The participants will initially be drawn from the 463 students enrolled in the Nuts4Brain-Z observational study (data collection September–December 2023) [58,59,60]. If necessary, recruitment will be extended to additional UCLM undergraduate students to reach the target sample size.

The sample size calculation was based exclusively on the primary outcome as we did not find previous studies examining the association between nut consumption and our secondary outcomes that would provide the necessary effect size estimates for power and sample size calculations. Consequently, the study should be considered exploratory with regard to these secondary outcomes, and any findings related to them should be interpreted with appropriate caution. While our sample size provides adequate power for detecting changes in the primary outcome, we acknowledge that it may be underpowered for detecting meaningful differences in secondary outcomes, particularly if the true effects are small to moderate in magnitude.

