### 2.5. Participant Recruitment

Following ethics approval, authorization will be obtained from university authorities at UCLM in Cuenca, Spain. Professors will be contacted to request 15 min of class time for a brief presentation about the study, during which flyers will be distributed. Interested students can provide contact information either by giving their mobile number or scanning a QR code to complete an online form. QR codes will also be available on posters throughout the university. A research team member will then contact interested students via WhatsApp LLC (Meta Way, CA, USA) to answer questions and, if they agree to participate, schedule the baseline visit. All participants will be instructed to avoid nut consumption for at least 7 days before the baseline assessment.

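### Nothing in eligibility, recruitment or randomisation keeps housemates out of different arms, although the protocol names shared housing as a contamination route; one screening question would largely close it

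*Protocol article*

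**What the plan says.** Section 2.12.1 of the protocol article (Limitations) names the route itself: "some control group participants may live with participants from other study groups, which makes complete prevention of contamination unrealistic". It adds that biweekly contact and vitamin E measurement do not prevent contamination of the control group.

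The sections where the route could be closed are silent on it:

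- **2.3 Eligibility.** The first inclusion criterion is "being enrolled as a university student in any undergraduate academic program at the University of Castilla-La Mancha (UCLM), campus of Cuenca". The other criteria cover age, consent, allergy, illness, availability and pregnancy. None concerns living with another participant.
- **2.5 Recruitment.** Students are approached through classes, flyers and posters on one campus. Then "A research team member will then contact interested students via WhatsApp LLC" to answer questions and book the baseline visit. No housing question is mentioned.
- **2.6 Randomisation.** Restriction is by sex only: "randomization will be stratified by sex considering the ratio of 2 males:3 females". Allocation is of individuals.

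The protocol does have safeguards. Nut-arm participants are told to eat only the supplied nuts, and controls to avoid nuts (2.7). All participants are messaged every two weeks (2.8). Unauthorised intake in controls is to be detected by a vitamin E rise of more than 5% or by self-report, and sensitivity analyses for potential bias are foreseen (2.12.2).

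**The concern.** Only the two nut arms receive nuts. They collect daily bags for a whole period at a time, with pick-ups at months 2 and 4 (2.7), so a participant's home can hold about two months of supply. If a control lives there, each portion passed on raises intake in one arm and lowers it in the other, and the contrast narrows from both sides.

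The safeguards act on behaviour or act afterwards. The 5% vitamin E trigger equals the bottom of the 5–15% rise that 2.8 quotes for regular intake of 30–80 g/day, so occasional sharing of smaller amounts could pass unnoticed. A control who is flagged still counts in the primary analysis, because 2.11 makes intention-to-treat primary. The dilution therefore stays in the main estimate whether or not it is detected.

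At stake is a bias towards no effect, and lost power, in a trial with little power to spare.

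**Working it through.** **1. The protocol's own figures (2.4).** Inputs: "A medium effect size (Cohen’s d = 0.5) and homogeneity of variance (σ = 1) were assumed across groups"; "With a two-sided α of 0.05 and 80% power (β = 0.20"; "the Benjamini–Hochberg correction was applied to control the false discovery rate"; power to detect at least one difference from control; "All three arms were allocated at a 1:1:1 ratio". The stated result is 42 per group, then 53 per group and 159 in total after 20% dropout.

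- Dropout step: 42 / 0.8 = 52.5, rounded up to 53; 53 × 3 = 159. This reproduces.
- The 42: simulating two z-statistics with a shared control (correlation 0.5) and the Benjamini–Hochberg rule gives about 70% power at 42 per group two-sided, and 54 per group for 80%. A one-sided 0.05 test gives 80% at 42. The stated 42 is therefore not reproduced on the stated two-sided basis. That is a separate matter; here it shows only that there is no reserve.

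**2. How often a shared home is split.** Take two-person households and independent 1:1:1 allocation. Given that one member is a control, the other is in the 30 g arm with probability 1/3. If a share s of participants live in such pairs, the share of controls living with a 30 g participant is f = s/3, and by symmetry the same share of the 30 g arm lives with a control. The protocol gives no s, so s = 10–30% is assumed:

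- s = 10%: f = 3.3%
- s = 30%: f = 10%

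**3. Loss of contrast.** Let g grams per day move from the higher-dose to the lower-dose housemate in each split pair (assumed 10–15 g). Controls gain f·g from 30 g housemates, and the 30 g arm loses f·g to controls. Controls and the 30 g arm each also gain f·g from 60 g housemates, which cancels. So

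contrast = 30 − 2·f·g

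| s | g (g/day) | f | 2·f·g (g/day) | Contrast (g/day) | Loss | d |
|---|---|---|---|---|---|---|
| 10% | 10 | 0.033 | 0.67 | 29.3 | 2.2% | 0.489 |
| 30% | 15 | 0.100 | 3.00 | 27.0 | 10% | 0.450 |

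Here d = 0.5 × contrast / 30, which takes the effect as proportional to dose. The 60 g versus control contrast is 60 − 4·f·g by the same reasoning, so its proportional loss is identical.

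**4. Power per contrast.** With 42 per arm, SE = √(2/42) = 0.218. Two-sided 0.05, unadjusted, power = Φ(d/SE − 1.96):

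- d = 0.50: Φ(2.291 − 1.96) = 63%
- d = 0.489: Φ(2.240 − 1.96) = 61%
- d = 0.45: Φ(2.062 − 1.96) = 54%

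**5. Same dilution on the protocol's criterion.** For at least one rejection after Benjamini–Hochberg at 42 per arm, with both contrasts diluted equally, two-sided power goes from 70% to 68–61%. On the one-sided basis that matches 42, it goes from 80% to 79–72%.

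**6. Extreme bound.** If every control living with either nut-arm participant (2s/3, so 6.7–20% of controls) obtained the whole treatment effect, d would be 0.467–0.40 and two-sided power on that criterion 64–51%. This is a ceiling, not an expectation.

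**7. Cost of one participant per household.** One replacement per pair: 159 × 0.10 / 2 ≈ 8 and 159 × 0.30 / 2 ≈ 24. The target of 159 is 34% of the first pool of 463 students, and 2.4 allows wider recruitment.

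**The case against.** The strongest reply is that this is a disclosed and partly managed limitation, with no contradiction or wrong figure behind it, and that the harm rests on an undocumented rate. Much of that stands. The text says that controls may live with other participants and that complete prevention is unrealistic. It does not say that they will, or that nothing can be done. Instructions, contact, detection and sensitivity analyses exist. The remedy is also imperfect: it relies on students knowing and disclosing that a flatmate is enrolled, it misses later moves, and it leaves classmates and friends. What the reply does not answer is that none of the existing measures removes the route from the primary contrast, and that a cheap one would.

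Three stronger readings are tempting and are not supported.

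- **A loss of 7–30%.** This follows from taking 10–30% as the share of controls living with a 30 g participant. Under 1:1:1 allocation in pairs that needs 30–90% of all participants to live with another participant, which nothing in the protocol suggests.
- **Household correlation is ignored in the analysis.** Section 2.11 names a repeated-measures mixed model without giving its random effects. That detail is commonly left to the analysis plan, which is not shown. For housemates split between arms, positive correlation would also reduce the variance of the difference between arms.
- **Flatmates will volunteer together.** The protocol does not say so. Section 2.4 draws participants first from an earlier observational cohort.

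Proportionality of effect to dose is also only an assumption: the Discussion expects a modest extra benefit at 60 g.

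**Conclusion.** The point holds as a design improvement of modest size. The protocol identifies shared housing as a way for controls to be exposed, and no step in 2.3, 2.5 or 2.6 prevents it. Any sharing biases the intention-to-treat contrasts towards the null. If 10–30% of participants live in two-person participant households and 10–15 g/day changes hands in split pairs, the 30 g versus control contrast loses about 2–10%, d falls to about 0.49–0.45, and per-contrast power falls from 63% to about 61–54%. These figures are illustrative: with few cohabiting participants or little sharing the loss approaches zero. The case for acting rests on the low cost of prevention before recruitment starts, not on a large expected loss.

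**What to change.** At the WhatsApp contact in 2.5, ask each volunteer whether they share a flat or room with someone already enrolled. Enrol only the first consenting member of that household. Add this as a criterion in 2.3, with a one-line definition of household that says how student residences are treated (for example, a shared flat or room and not a whole building), and amend 2.12.1 to say that this route is restricted by design.

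The cost is one question, one eligibility line with ethics approval, and a few volunteers turned away: about 8–24 replacements under the assumption above. The Introduction describes the article as written before recruitment, so the change is still open; once housemates have been randomised apart it is not. Sharing among classmates, bought nuts and participants who move in together later would remain, so the instructions and monitoring should stay. Giving all members of a household the same arm is an alternative that turns nobody away, but it makes the household the unit of allocation for those participants and the analysis would have to reflect that.
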